### **Randomization and blinding**

Kebeles' will be the randomization unit whereas the observation or analysis units will be the individual study participants. The selected 16 non-adjacent Kebeles will be listed alphabetically. A restricted randomization with a 1:1 allocation will be used to assign the Kebeles to the intervention or control groups. In Microsoft Excel 2010, a list of random numbers will be created, and the generated values will be fixed by copying them as "values" next to the alphabetic list of the Kebeles. The first eight will be chosen as intervention clusters, and the last eight will be chosen as control clusters, in ascending order based on the produced random numbers. Moreover, a statistician who is blind to the study groups and is not involved in the research will create the allocation sequence and randomize the clusters. The allocation of Kebeles to the intervention or control groups will be hidden from the data collectors or outcome assessors.

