## Sample size calculations

The Hooper and Bourke method for cluster randomization studies of parallel arms with repeated cross-sections is used to calculate the sample size. To illustrate within intraclass correlation coefficient (ICC) and between ICC, the technique comprises the measurement of two design effects, with the product of the two being used to inflate the sample size for individual randomization. The within ICC is the correlation between any two pregnant women in the same cluster, while the between ICC is the correlation between any two pregnant women in different clusters. The first design effect ( $d_c$ ) attributable to cluster randomization is measured using a within ICC of 0.05 obtained from a community-based cluster randomized trial in Ethiopia. The design effect ( $d_c$ ) is calculated as:

$$d_c = 1 + (m - 1)\rho$$

Where  $m$  is the cluster size assumed to be 20 (i.e., the total number of pregnant women who will be questioned in each cluster) and  $\rho$  is the within ICC.

The second design effect ( $d_r$ ) attributable to repeated evaluations (baseline/endline) is calculated by using the within ICC and a cluster autocorrelation coefficient ( $\pi$ ) of 0.80.

The second design effect ( $d_r$ ) is calculated as:

$$d_r = (1 - r^2)$$

Where  $r = \left( \frac{m\rho\pi}{d_c} \right)$

The required sample size is then calculated by multiplying the ‘sample size assuming individual randomization’ by both design effects ( $d_c$  &  $d_r$ ). It is calculated as:

$$n = \left[ \frac{(a+b)^2 * (p_1 q_1 + p_2 q_2)}{(p_1 - p_2)^2} \right] * d_c d_r$$

Where:

$n$  represents the sample size in each of the arms i.e., intervention and control

$a$  represents conventional multiplier (1.96) for alpha ( $\alpha = 0.05$ ) and  $b$  represents conventional multiplier (0.842) for power ( $1 - \beta = 0.80$ )

$p_1$  represents proportion of post-intervention users of MWH and  $q_1$  represents proportion of post-intervention non-users of MWH.

$p_2$  represents proportion (50%) of users of MWH taken from a study in Gurage Zone, Southwest Ethiopia  and  $q_2$  represents pre-intervention proportion of non-users of MWH.

$|p_1 - p_2|$  *an effect size* - is an absolute change in proportion of MWH utilization after intervention. It is estimated to be 20%.

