In addition, the following parameters are considered: 95% CI, 80% power, 1:1 allocation ratio of intervention to control, 10% potential loss to follow up, and tabulated sample size ( $n_0 = 199$ ) required to detect a difference in two proportions at 5% significance level with 80% power in literature.  According to Hooper and Bourke, the number of clusters (K) for the sample is determined using the formula  $K = (n_0 d_c d_r) / m$ . The final sample size is calculated by substituting the specified values into the above formula. Hence, a total of 16 clusters are needed, with an approximated final sample size of 320 couples. The two arms each will have 160 couples (pregnant women with their male partners).

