### **Participants' selection**

Hadiya Zone was one of lowest performers in SNNPR regarding MWH use in 2021. This situation drew the attention of the researchers to perform this study in this area. First, health centers with functional MWHs will be identified based on the MWH functionality criteria adopted from national guideline. During the assessment; the availability of staff, beds for sleeping, water supply, kitchen and cooking utensils, bathrooms, and latrines will be considered as crucial to declare the functionality of MWHs.

In Ethiopian health system, one health center serves an estimated 25,000 population with a catchment of five Kebeles (clusters). Each Kebele contributes 5000 population. Secondly, all the Kebeles under each health center catchments will be listed. Thirdly, all non-adjacent Kebeles relatively from the health centers will be identified. Next, 16 non-adjacent Kebeles will be chosen. At least one cluster (Kebele) will be left between non-adjacent Kebeles, and this will serve as a buffer zone.

The selected 16 non-adjacent Kebeles will be randomly assigned to intervention and control groups using simple randomization. Census and/or health post records will be used to identify pregnant women. Then, women will be asked their Last Menstrual Period (LMP) to estimate the gestational age. Women who are in the beginning of second trimesters (14 -16 weeks of gestation) will be listed. This list will be used as a sampling frame. The study participants will be selected from each Kebele using simple random sampling technique.

Participants who consent to involve in the study with their male partners (husbands) will be included in the study. Women and their male partners will be requested to sign an informed consent to ensure voluntary participation. Once consent is obtained, each participant will be interviewed to complete a baseline survey. The baseline questionnaires contain socio-demographic and obstetrics characteristics, health services including MWH use, paternal and maternal knowledge and attitude, and male partner involvement.

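### The Kebele allocation restricts only arm size (8:8) and is mislabelled as simple in one section; balancing the draw on prior MWH use and adjusting for it would be a cheap gain in precision

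*Protocol*

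**What the plan says.** Two sections of the Protocol describe the same allocation.

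- **Participants' selection:** "The selected 16 non-adjacent Kebeles will be randomly assigned to intervention and control groups using simple randomization".
- **Randomization and blinding:** "A restricted randomization with a 1:1 allocation will be used to assign the Kebeles to the intervention or control groups". The mechanism is then given. The Kebeles are listed alphabetically, Excel random numbers are attached and fixed, and the list is ordered by those numbers. Then: "The first eight will be chosen as intervention clusters, and the last eight will be chosen as control clusters". A statistician outside the research, blind to the groups, does this.

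No section names a stratum, a matched pair or a balance criterion. Sampling procedure says only that the clusters are assigned at random.

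Other parts of the Protocol bear on the point:

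- Participants' selection lists MWH use among the contents of the baseline questionnaire.
- Trial activity schedule puts screening, consent, allocation and baseline data collection all in September and October 2022, with the intervention starting in November.
- Primary outcome and Statistical analysis measure the effect as a difference-in-differences. Sampling procedure says the same participants are assessed at both times.

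**The concern.** The two labels name different methods. Simple randomization in the strict sense does not guarantee equal arms. The Excel steps do, and they guarantee nothing else.

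A reader who meets the word restricted may credit the design with covariate balance that it does not have. With eight Kebeles per arm, prior MWH use is left to a single draw, although the baseline survey collects it.

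What is at stake is precision, and how convincing the baseline table looks. The validity of the randomization is not in question.

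**Working it through.** **Inputs, all from Sample size calculations:** 16 clusters, m = 20, within ICC ρ = 0.05, cluster autocorrelation π = 0.80, MWH use p = 0.50, target difference 20 points, n0 = 199.

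**1. The plan's own figure.**
- d_c = 1 + 19 × 0.05 = 1.95
- r = 20 × 0.05 × 0.80 / 1.95 = 0.41
- d_r = 1 − 0.41² = 0.83
- n0 × d_c × d_r = 199 × 1.622 = 322.7, and 322.7 / 20 = 16.1 clusters

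This reproduces the stated 16 clusters and about 320 couples.

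**2. The labels.** There are C(16,8) = 12,870 possible 8:8 splits, and the Excel procedure makes them equally likely. Independent coin flips would give exactly 8:8 with probability 12,870 / 65,536 = 19.6%, and 5:11 or worse with probability 21%. The procedure therefore fits the label restricted (to equal arm size) and not the label simple.

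**3. Chance imbalance in level.**
- Between-Kebele SD of underlying use = √(0.05 × 0.50 × 0.50) = 11.2 points.
- SD of the difference between two means of eight = 11.2 × √(2/8) = 5.6 points. A gap above 5.6 points has probability 32%, and one of 10 points or more has 7%.
- For observed baseline rates, SD = √(0.25 × 1.95 / 20) × √(2/8) = 7.8 points. An observed gap of 10 points or more, half the target effect, arises in about 20% of draws.

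**4. What difference-in-differences leaves.**
- SD of the change in a Kebele's underlying rate = √(2 × (1 − 0.80) × 0.05 × 0.25) = 7.1 points.
- SD of the arm difference = 7.1 × √(2/8) = 3.5 points. A residual above 5.6 points has probability about 11%.

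**5. Sensitivity (assumed ranges).** With p from 0.20 to 0.50 and ICC from 0.02 to 0.10, the SD in level runs from 2.8 to 7.9 points. Multiplying by √(2 × 0.20) = 0.632 gives 1.8 to 5.0 points after differencing.

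**6. What balancing or adjusting gains.** Take the variance of an unadjusted endline comparison as 1, with r the baseline-endline correlation of cluster means.
- Plain difference-in-differences: 2(1 − r) = 2 × 0.59 = 1.18
- Baseline adjusted for, or exactly balanced: 1 − r² = 0.83
- Ratio: 1.18 / 0.83 = 1.42

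The gap is (1 − r)², so it is never negative. The value 0.83 is the d_r of step 1, so the sample size already assumes the adjusted analysis. When the observed baseline means are equal, the difference-in-differences equals the endline difference, so balancing pushes the estimate in the same direction as adjustment.

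**7. Limit of the gain.** With 20 women per Kebele, the observed rate has reliability 20 × 0.05 / 1.95 = 0.51 for the underlying rate. Perfect balance on the observed rate would leave an underlying level SD of about 5.6 × √(1 − 0.51) = 3.9 points. A simulation of randomizing within two or four strata of prior use agrees in direction. The chance of an observed gap of 10 points or more falls from about 21% to 4% and 0.2%. The chance of an underlying gap that large falls from about 7% to 3% and 2%.

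**The case against.** The opposing case is strong, and most of it stands.

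- **The label clash changes nothing operationally.** Randomization and blinding gives a complete procedure, and fixing 8:8 is a form of restriction. A reader might infer that the allocation method is undefined. It is not: one word in Participants' selection is loose.
- **Chance imbalance is not bias.** The 5.6-point SD is the between-cluster variance that d_c = 1.95 already inflates the sample for.
- **The planned estimator removes part of it.** A reader might take a gap above 5.6 points, 28% of the 20-point target, as an error that reaches the primary estimate in one trial in three. That describes levels. After differencing, the corresponding probability is about 11%.
- **Distance is not shown to be available.** A reader might assume that walking time can be balanced at once. Eligibility sets a threshold of two hours' walk, with limited transport as an and/or alternative, and the listed questionnaire contents do not name walking time. The Protocol gives no between-Kebele spread for it.
- **The largest variance is used.** The Protocol calls the Zone one of the lowest performers in MWH use. At an assumed 20% use the level SD is 4.5 points.

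On the other side, differencing does not make balance or adjustment pointless. At r = 0.41 it is noisier than ignoring baseline altogether (1.18 against 1). The planned chi-square comparison, which has no stated baseline adjustment, carries the full imbalance in level.

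**Conclusion.** The point holds as a cheap improvement together with a wording correction. The procedure restricts arm size only, and simple is the wrong word for it. Leaving out covariate constraints is neither an error nor a source of bias, and the documents do not support a claim that it undermines the result.

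At p = 0.50 and ICC 0.05, the chance difference in underlying use has an SD of 5.6 points in level and about 3.5 points after difference-in-differences with autocorrelation 0.80. The gain from balancing and adjusting is a move in relative variance from 1.18 towards 0.83.

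This rests on the protocol's r, which comes from a repeated cross-section formula. Because the same women are assessed twice, the true r may be higher and the gain smaller: at an assumed r = 0.60 the comparison is 0.80 against 0.64. It also takes baseline use to mean use at the previous birth. That follows from enrolment at 14–16 weeks and the requirement of a birth in the last five years.

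**What to change.** 1. In Participants' selection, replace the simple-randomization label with the wording of Randomization and blinding, and say in both places what is restricted.
2. Within the September–October 2022 window, complete baseline in all 16 Kebeles before allocation. Reorder Participants' selection and Sampling procedure to match, since both now describe assignment before women are listed and sampled. Recruitment then also finishes before allocation is known.
3. Have the independent statistician enumerate the 12,870 splits and keep those balanced on Kebele-level MWH use at the previous birth, under a criterion written down beforehand. Retain several hundred or more, and draw one at random.
4. Adjust for baseline MWH use in the primary model.
5. Add distance as a constraint only if walking time is recorded as a number at screening.

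**Cost:** no extra clusters or couples. Allocation must wait for entered baseline data from all 16 Kebeles, which tightens the run-up to the November start. The model loses a degree of freedom or two, which counts for something with 16 clusters.

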### **Information contamination reduction**

The study participants in the control group may be informed about the intervention in various social occasions such as weeding, marketing, or funeral ceremony. This may affect intervention outcome unfavorably. Therefore, leaving at least one cluster (Kebele) between non-adjacent clusters may reduce such contamination.

### **Brief description of the intervention**

The intervention has three components: group health education, provision of take-home print health messages, and home visits. The study participants in the intervention group will receive the intervention alongside the usual care. The couples will receive the intervention together. The intervention will be provided at three contact points. The first contact will be the group health education at baseline whereas the second, and third contacts will be home visits. The control group will receive the usual care.

### **Implementation of the intervention**

The intervention will be provided to the couples in the intervention group. Group health education, provision of leaflets (print health messages), and home visits will be conducted. Health education will be provided once in the first month whereas the home visits will be performed two times at two months intervals (i.e., at 3rd and 5th months). Print health messages will be provided three times (i.e., at first contact during health education and at each of the two home visit).

The health education session will be provided in a group for 90-120 minutes. All participants in the intervention within a Kebele will be gathered at one common place and receive health education. Health extension workers and Kebele leaders will select the place of health education and invite the participants. Both women and their male partners will be invited to receive the health education. This will be done in all eight intervention Kebeles, and as a result, eight health education sessions will be performed at baseline.

Health education will address the importance and kinds of paternal support, and purpose and benefits of staying in MWHs. The services available at MWHs, the benefits of staying at MWHs, the right time to visit MWHs, and the importance of paternal support will be discussed. Types of paternal support during pregnancy and MWH stay, such as allowing a spouse to stay at MWH, accompanying her to MWH, providing financial support during MWH stays, providing food and other necessary materials, looking after the home, and caring for the remaining children at home,

will be addressed. Health messages in leaflets focus on paternal support and the purpose and advantages of MWHs. Next, the schedule of home visits will be proposed through discussions with participants, with an emphasis that both women and their male partners will be contacted at their residence.

The first home visit will be conducted two months after the health education intervention (i.e., in the 3rd month of the intervention). During this visit, both women and their male partners will receive advice regarding antenatal care, paternal support, and MWHs. Male partners will be advised on how to support their wives and encourage them to use antenatal care, stay at MWHs, and deliver at a health facility. The couples will be asked to discuss their perceptions of antenatal care, MWH use, and health facility delivery. Based on their perceptions and actual observed practices, they will be advised. Leaflets with the same health messages at baseline health education will be provided. Repeated visits will be made if the couple is absent.

The second home visit will be conducted two months after the first home visit (i.e., in the 5th month of the intervention). During this visit, paternal support, birth preparedness plans, and intention to use MWH will be assessed. Leaflets containing messages regarding possible risks of home delivery and advantages of staying at MWHs and institutional delivery will be provided. Any misunderstandings regarding MWHs will be clarified through discussion. Male partners will be advised to continue supporting their wives. The expected delivery date will be estimated and a possible appointment to arrive at the MWH will be made. To make the woman and her partner remember the appointment, a written invitation letter will be provided. However, the woman will be advised to attend antenatal care, follow the advice of health professionals, and come to a health facility if she feels any illness (Table 1).

**Table 1:** Details of intervention activities

| Intervention packages | List of activities                                                                                                                                                                                                                                                                                                                                                                                                                                                                                                                                                                                                                                                                                                                                                                                                                                                                                                                                                                                                                                                                                                                                                                                                                                                                                                   | Duration          | Responsible body          |
|------------------------------|-----------------------------------------------------------------------------------------------------------------------------------------------------------------------------------------------------------------------------------------------------------------------------------------------------------------------------------------------------------------------------------------------------------------------------------------------------------------------------------------------------------------------------------------------------------------------------------------------------------------------------------------------------------------------------------------------------------------------------------------------------------------------------------------------------------------------------------------------------------------------------------------------------------------------------------------------------------------------------------------------------------------------------------------------------------------------------------------------------------------------------------------------------------------------------------------------------------------------------------------------------------------------------------------------------------------------------|--------------------------|----------------------------------|
| Group health education       | 
Focus of health education
 
 
✚ Purposes and benefits of staying in MWHs 
 
- Explain what MWH is
 
- Purposes of MWH
 
- Types of services available at MWHs
 
- Benefits of staying at MWHs
 
- Who should use MWHs
 
- When to go to MWH
 
 
 
✚ Benefits and kinds of paternal support 
 
- Define what does paternal support mean in the current context (Hint: In this particular context paternal support refers to any kind of physical, material, or emotional support a husband provides to his expectant wife.)
 
- Emphasis on paternal support related to MWHs and discuss types of paternal support such as allowing a spouse to stay at MWH, accompanying her to MWH, providing financial support during MWH stays, providing food and other necessary materials, looking after the home, and caring for the remaining children at home etc.
 
 
 
✚ Provide leaflet to each couple at the end of the health education sessions 
 
- The health messages in the leaflets will focus on paternal support, and the purpose and advantages of MWHs.
 
 
 
 | 90-120 minutes per group | Trained Health Extension Workers |

|                   |                                                                                                                                                                                                                                                                                                                                                                                                                                                                                                                                                                                                                                                                                                                                                                            |                          |                          |
|-------------------|----------------------------------------------------------------------------------------------------------------------------------------------------------------------------------------------------------------------------------------------------------------------------------------------------------------------------------------------------------------------------------------------------------------------------------------------------------------------------------------------------------------------------------------------------------------------------------------------------------------------------------------------------------------------------------------------------------------------------------------------------------------------------|--------------------------|--------------------------|
| First home visit  | 
During first home visit:
 
 
✚ Assess the couples practice regarding antenatal care and paternal support
 
✚ Advise the MPs on how to support their wives during pregnancy
 
✚ Tell MPs to encourage their wives to use antenatal care
 
✚ Further, ask the couples to discuss their perceptions of antenatal care and paternal support and MWH use
 
✚ Advise them based on their perceptions and actual observed practices
 
✚ Provide them leaflets (same leaflet provided at baseline)
 
                                                                                                                                                                                         | 30-45 minutes per couple | Health Extension Workers |
| Second home visit | 
During second home visit:
 
 
✚ Assess the practice of paternal support and couples intension related to MWH use
 
✚ Assess any birth preparedness plans including readiness to use MWHs, financial preparations, transportation arrangements to MWH, and choice of place of delivery.
 
✚ Discuss the possible risks of home delivery and advantages of staying at MWHs and institutional delivery
 
✚ Clarify any misunderstandings regarding MWHs through discussion
 
✚ Advise the MPs to continue supporting their expectant wives
 
✚ Estimate the expected delivery date and make possible appointment to go to the MWH
 
✚ Provide them a written invitation to MWH
 
 | 30-45 minutes per couple | Health Extension Workers |

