### **Eligibility criteria**

The study participants will be couples living together where the women are pregnant in the beginning of second trimesters of pregnancy (14-16 weeks of gestation) and had given birth in the last 5 years before the current pregnancy, permanent residents of the study area, living  $\geq 2$  hours of walking distance from the nearest health facility and/or have no or limited access to public transportation, and are willing to participate in the study.

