## **Compliance parameter**

The number of participants who attended health education at baseline and contacted at the two home visits will be used to determine the participants' compliance with the intervention. We will use attendance sheets to determine participants' compliance with the proposed intervention packages. However, for various reasons, the participants in the intervention may not comply with the intervention. This may have undesirable effects on women's use of MWHs. This will be considered a dose-response function during the data analysis (Table 2).

**Table 2:** Summary of the trial protocol

| Content of intervention                  | Dosage  | Frequency | Duration | Compliance parameter                                   |
|-------------------------------------------------|----------------|------------------|-----------------|---------------------------------------------------------------|
| Group health education at baseline and leaflets | 90-120 minutes | Once             | One month       | Number of participants attended the health education sessions |
| Home visits and leaflets                        | 30-45 minutes  | Twice            | Two months      | Number of participants contacted at home visits               |

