### **Trial activity schedule**

The eligibility screening, obtaining informed consent, participant allocation, and baseline data collection will be performed in the months of September and October 2022. The actual intervention will be performed from November 2022 to April 2023. Then the endline data collection will be conducted two-weeks after the completion of the intervention, i.e., after May 15, 2023.

Accordingly, the participants' enrollment, intervention, and assessment schedule is summarized as follows (Table 3).

**Table 3:** Schedule of enrolment, interventions, and assessments

|               |                             |                        | STUDY PERIOD                            |                |                |                |                |                |                   |
|---------------|-----------------------------|------------------------|-----------------------------------------|----------------|----------------|----------------|----------------|----------------|-------------------|
|               |                             | Enrolment & Allocation | Post-allocation
(Intervention Phase) |                |                |                |                |                | Close out         |
| Time point    |                             | t (-1)      | t 1                          | t 2 | t 3 | t 4 | t 5 | t 6 | t (+1) |
| Enrolment     | Eligibility screen          |                        |                                         |                |                |                |                |                |                   |
|               | Informed consent            |                        |                                         |                |                |                |                |                |                   |
|               | Allocation                  |                        |                                         |                |                |                |                |                |                   |
| Interventions | Health Education + Leaflets |                        |                                         |                |                |                |                |                |                   |

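### The only contact that books the maternity waiting home stay is fixed to trial month 5, so for earlier enrolees it can fall inside or after the waiting-home window.

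*Protocol*

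**What the plan says.** Women must be at the "beginning of second trimesters of pregnancy (14-16 weeks of gestation") when listed (Protocol, Eligibility criteria; Participants' selection). The dates are fixed as follows: "The eligibility screening, obtaining informed consent, participant allocation, and baseline data collection will be performed in the months of September and October 2022", and "The actual intervention will be performed from November 2022 to April 2023" (Protocol, Trial activity schedule).

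Under Implementation of the intervention, each intervention Kebele has one group session in month 1. The first home visit follows two months later, and "The second home visit will be conducted two months after the first home visit", in month 5. Counting November 2022 as month 1, these are January and March 2023.

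The booking tasks sit at the second visit only. The text says "The expected delivery date will be estimated and a possible appointment to arrive at the MWH will be made", with a letter to help the couple remember. Table 1 lists the same tasks there ("Provide them a written invitation to MWH") and not under the first visit or the group session.

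Description of important terms and measurement places MWH stay in the final 2-3 weeks of gestation and counts a stay of one day as use. Compliance parameter measures home-visit dose as "Number of participants contacted at home visits".

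**The concern.** The contacts follow the trial calendar, while the MWH window follows each woman's pregnancy. Recruitment lasts two months and the window lasts two to three weeks, so one fixed visit month cannot suit everyone unless the slack is planned for. No section brings the second visit forward for women who are further along.

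The primary outcome is MWH use. A booking visit after birth cannot change it, and one at 37 weeks or later leaves little time to act. Under intention-to-treat, these women still count in the intervention arm, so the effect of the booking component is diluted. The error is towards no effect; it does not favour the intervention.

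A second consequence concerns the planned dose-response analysis. The compliance measure counts contacts at home visits with no condition on delivery, so as written a visit after birth counts as dose received.

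**Working it through.** **Inputs.** Gestation at listing 14-16 weeks (Eligibility criteria). Listing 1 September to 31 October 2022, and second visit in month 5, 1 to 31 March 2023 (Trial activity schedule; Implementation of the intervention). Window from 37-38 weeks (Description of important terms, taking term as 40 weeks; the 40 is an assumption).

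**The protocol's calendar.** Month 1 (November) + 2 = month 3 (January); + 2 = month 5 (March). It is internally consistent.

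**Formula.** Gestation at visit = gestation at listing + (visit date − listing date)/7.

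**Bound that needs no listing pattern.** From 14 to 37 weeks is 23 × 7 = 161 days, and 21 September 2022 + 161 days = 1 March 2023. A woman listed on or before 21 September is therefore at 37 weeks or more on every March date, even if listed at the minimum gestation and visited on the first day.

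**Individual cases.**

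| Listed | Weeks at listing | Reaches 37 weeks | Due (40 weeks) | Weeks on 1 March | Weeks on 31 March |
|---|---|---|---|---|---|
| 1 Sept | 14 | 9 Feb | 2 March | 39.9 | 44.1 |
| 1 Sept | 16 | 26 Jan | 16 Feb | 41.9 | 46.1 |
| 1 Oct | 14 | 11 March | 1 April | 35.6 | 39.9 |
| 1 Oct | 16 | 25 Feb | 18 March | 37.6 | 41.9 |
| 31 Oct | 14 | 10 April | 1 May | 31.3 | 35.6 |
| 31 Oct | 16 | 27 March | 17 April | 33.3 | 37.6 |

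Values beyond about 42 weeks mean that the woman has already delivered.

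**Shares.** The protocol gives no distribution of listing or visit dates, so these rest on assumptions: gestation uniform over 14-16 weeks, and dates even within the ranges shown.

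| Listing | Visit | ≥37 weeks | ≥38 weeks | ≥40 weeks |
|---|---|---|---|---|
| 1 Sept-31 Oct | 1-31 March | 69.6% | 58.2% | 35.3% |
| 1 Sept-31 Oct | 1-8 March | 50.8% | 39.3% | 16.4% |
| September only | 1-31 March | 98.7% | 93.8% | 68.2% |
| October only | 1-31 March | 41.4% | 23.8% | 3.4% |
| October only | 1-8 March | 8.0% | 0.6% | 0.0% |
| 17-31 Oct | 1-31 March | 17.1% | 4.4% | 0.0% |
| 17-31 Oct | 1-8 March | 0% | 0% | 0% |

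If eligibility runs to 16 weeks 6 days, the first row becomes 74.9%, 63.9% and 41.0%.

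**The January visit, for comparison.** With even listing and visits over January, gestation runs from 22.9 to 37.7 weeks and 0.1% are at or past 37 weeks (0.9% if 16 weeks 6 days is eligible).

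**The case against.** The strongest counter-reading is that 14-16 weeks applies at the group session, which the protocol elsewhere describes as being at baseline. A woman at 14-16 weeks on 1 November would be at 31.1 to 37.4 weeks during March, and the problem would largely vanish. However, the activity schedule puts screening and baseline data collection in September and October, and gestation is assessed when women are listed. The design works only if recruitment is late, and nothing requires that.

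The protocol also says that visit times will be discussed with participants. That may set the day, but the months stay fixed and nothing directs staff to look at gestation.

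Three points stand and limit the concern:

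- The 37-week threshold is the opening of the window, not its end. A one-day stay counts as use, so a visit at 37-39 weeks can still work. In the base case about half of the 70% are still short of 40 weeks, and being past 40 weeks is not the same as having delivered.
- Much of the message arrives earlier. The November session covers when to go to an MWH, and the January visit encourages its use. What comes late is the dated appointment and the letter.
- The shares depend on an unknown listing pattern, so the size of the dilution in MWH use cannot be derived from the protocol.

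It can also be said that the coding of a visit after delivery belongs in the analysis plan. The detail may, but the compliance definition is stated in the protocol and carries no condition on delivery.

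**Conclusion.** The concern holds. On the protocol's own dates, every woman listed by 21 September is already at or past 37 weeks at the only contact that books her stay, and some are past their due date. How many women this affects depends on recruitment: about 70% at or past 37 weeks if listing and visits are spread evenly, and anywhere from 0% to 99% under other patterns. Late-October enrolees visited in early March are in time, so the schedule can work, but the plan does not secure it.

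The comparison between arms remains valid for the package as scheduled. The loss is partial dilution towards no effect on the primary outcome, plus a dose measure that can count contacts made too late to matter. This should be fixed, but it does not undermine the trial.

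**What to change.** Amend Implementation of the intervention and Table 1 so that the delivery-date estimate, the MWH appointment and the invitation letter are given at the January visit, and repeated in March for women still pregnant. The estimate need not wait for month 5, because at listing "Then, women will be asked their Last Menstrual Period (LMP) to estimate the gestational age". Record gestational age and delivery status at every contact, and amend Compliance parameter so that the second visit counts as dose received only if it took place before delivery.

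This is a text amendment that adds no contacts or participants; under the protocol's own amendment rule it needs ethics board approval first. Its drawback is that late-October enrolees get the appointment early, at about 23-29 weeks, which is why the March repeat is needed.

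An alternative is to time the second visit at 32-35 weeks. That window runs from 22 December 2022 (listed 1 September at 16 weeks; 16 December if 16 weeks 6 days is eligible) to 27 March 2023 (listed 31 October at 14 weeks), inside the intervention period. It is less clean: for early-September enrolees the first visit must move earlier and the two-month spacing is lost, and scheduling within a Kebele becomes less uniform.
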